### Analyses

Analyses of data collected from phase two (the pilot RCT) will be descriptive with key outcomes being interval estimates of the variables of interest relating to assessment of acceptability, feasibility and data completeness. Although we may not have the power to detect a clinically important difference between groups we will generate interval estimates of the mean difference between groups for the main outcome measures to be included in a definitive trial (for example, PA and HbA1c). This will allow us to test the appropriateness of our analytic procedures. As this is a pilot study, the level of missing data will be documented but no imputation will be undertaken. Since we can not rule out the possibility of a very large difference between groups, the outcome of the analyses may suggest that a larger trial is not required. Planned exploratory sub-group analyses will be conducted to determine whether differences exist between primary healthcare professionals based on role and between patients as a function of gender, age, method of diabetes control and length of time since diagnosis of Type 2 diabetes.

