### Sample size

A total of 200 patients will be recruited from up to 20 primary care practices in the County Durham and Darlington area of North East England. The final number of practices will be identified following completion of phase one (open pilot) where an assessment of practice recruitment and retention rates will be conducted, with reference to practice list size (with three cut-off points: <3,280; ≥3,280 to 5,989; ≥5,990 to 10,453; and >10,454); the number of patients fulfilling the eligibility criteria and the number of patients recruited per practice. Up to 10 practices will be randomised to MaMT2D and a further 10 to usual clinical care. Although the trial is not powered for a definitive analysis, exploratory analyses examining between group differences will be reported based on a calculation of physical activity behaviour and HbA1c. The data generated from the pilot RCT including an estimate of the intra-cluster correlation co-efficient [47] will facilitate a power calculation to inform a definitive RCT if acceptability, feasibility and fidelity are demonstrated.

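### The analysis section leaves open dropping the definitive trial because of a very large pilot difference, which conflicts with the pilot's stated purpose and cannot be supported by its design

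*Protocol article*

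**What the plan says.** The article describes the purpose of the between-group comparison in two places.

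- **Phase two, Sample size.** "Although the trial is not powered for a definitive analysis, exploratory analyses examining between group differences will be reported". The data, including an estimate of the intra-cluster correlation, are to feed a power calculation for a definitive trial "if acceptability, feasibility and fidelity are demonstrated". The size is given as "A total of 200 patients will be recruited from up to 20 primary care practices", and "Up to 10 practices will be randomised to MaMT2D and a further 10 to usual clinical care".
- **Phase two, Analyses.** "Analyses of data collected from phase two (the pilot RCT) will be descriptive". The section concedes limited power ("Although we may not have the power to detect a clinically important difference between groups") and says that interval estimates for the main outcomes, with physical activity and HbA1c as examples, will show whether the analytic procedures are suitable. It then adds that, since a very large difference cannot be excluded, "the outcome of the analyses may suggest that a larger trial is not required".

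The phase two Objectives do not include testing effectiveness. The primary objectives concern recruitment, retention, fidelity and process evaluation. The secondary objectives concern variability and interval estimates.

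**The concern.** Everywhere else the pilot's effect estimates are planning information. This one sentence gives them a second use: a large enough difference could be a reason not to run the definitive trial. The Objectives and Sample size sections make no provision for that use.

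At stake is the trial that the pilot exists to inform. If a striking estimate appears, the protocol could be cited as having foreseen that no further trial was needed. The estimate would then be doing a definitive trial's work, from a study that says it is not one and whose design leaves room for bias that a confidence interval does not show.

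**Working it through.** The article gives no power, standard deviation, intra-cluster correlation (ICC) or target difference behind the 200 patients, so it has no figure to reproduce. The check has two parts.

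**1. What a large difference would rest on**

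| Feature | Where stated | Consequence |
|---|---|---|
| Practices are randomised before their patients are identified and invited; the two arms have different patient information sheets | Recruitment procedures (phase one, applied unchanged to phase two) | Who consents can differ by arm. A narrower interval would not remove this |
| Participants and researchers are not blinded | Blinding | Behaviour, self-report and assessments made by practice staff can differ by arm |
| At most 20 practices; 11 randomised at submission | Phase two, Sample size; Trial status | Few clusters, so chance imbalance between arms is likely |
| Main outcomes named only as examples; intervals at each time point | Phase two, Analyses; Discussion | It is not settled which estimate would be the very large one |

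**2. Precision, using HbA1c**

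Inputs from the article: 200 patients, up to 20 practices, equal allocation by practice, 95% intervals. The Background section on the intervention reports a review that took an HbA1c reduction of at least 0.3% as clinically effective.

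Assumptions not in the article: HbA1c standard deviation (SD) 1.0 to 1.5 percentage points, ICC 0.01 to 0.10, equal cluster sizes, no dropout, no gain from baseline adjustment.

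- Average cluster size: m = 200/20 = 10.
- Design effect: DE = 1 + (m − 1) × ICC.
- Standard error of the difference: SE = SD × √(4 × DE/200).
- Half-width: t × SE, with t = 2.101 on 20 − 2 = 18 degrees of freedom.

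| SD | ICC | DE | SE | 95% half-width |
|---|---|---|---|---|
| 1.0 | 0.01 | 1.09 | 0.148 | 0.31 |
| 1.0 | 0.05 | 1.45 | 0.170 | 0.36 |
| 1.0 | 0.10 | 1.90 | 0.195 | 0.41 |
| 1.5 | 0.01 | 1.09 | 0.221 | 0.47 |
| 1.5 | 0.05 | 1.45 | 0.255 | 0.54 |
| 1.5 | 0.10 | 1.90 | 0.292 | 0.61 |

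The half-width is therefore at least as large as the 0.3% criterion throughout, and about twice it at the upper end. For an interval to lie wholly beyond 0.3%, the estimate would have to be about 0.3 + 0.31 = 0.61 to 0.3 + 0.61 = 0.91 points, or two to three times the criterion.

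If the 200 patients came from only 11 practices (m = 18.2, 9 degrees of freedom, arms treated as equal), the same formulas give half-widths of about 0.35 to 0.79.

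**The case against.** **The wording is hedged, and the article labels the comparison properly elsewhere.** The sentence says only that the analyses may suggest something, and the statistician is blind to allocation. The accelerometer shows patients no data. All this is true, and it lowers the severity. It does not explain what the sentence is for. If the intervals are descriptive, no trial decision should hang on them.

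**Low power does not invalidate an interval.** A single pre-named, cluster-adjusted interval lying wholly beyond a pre-set large effect would be real evidence of a difference. That stands. But the sentence is tied to no such interval, and bias from recruiting after allocation would remain however wide the gap.

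**The missing threshold, outcome and time point may be in an analysis plan that is not shown.** That is fair, and their absence alone is no finding. The point rests on the inference that the article states and on its conflict with the Sample size section.

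A reader might infer more than the article supports:

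- *That multiple intervals make a false decision likely.* Six independent 95% intervals (two outcomes, three follow-ups) give 1 − 0.95^6 = 26% for at least one excluding zero under no effect. But the sentence speaks of a very large difference, not of excluding zero. Suppose that means 0.64 points, twice the 0.32% pooled effect in the Background. With SD 1.2 and ICC 0.05 (SE 0.204), the chance of a favourable estimate that large under no effect is about 0.3% per look, and about 2% over six independent looks. Counting every outcome at every visit goes further astray, since the sentence follows on from the main outcomes.
- *That a null result would end the programme.* Nothing in the article says so.
- *That only overestimates could look very large.* This is untrue if the true effect is very large, which is the case the sentence describes.
- *That an effectiveness claim is planned.* The sentence does not state a direction, and effectiveness is not an objective.

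**Conclusion.** The point holds in a limited form. One sentence allows a pilot effect estimate to bear on whether the definitive trial is run. That conflicts with the descriptive label in the same section and with the Sample size section, which disclaims definitive power and ties the next trial to acceptability, feasibility and fidelity. The conflict is in the text and needs no assumption.

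That a large difference could not settle the matter follows mainly from the design: recruitment after allocation, no blinding of participants or researchers, and few clusters. The precision figures support this but depend on the assumed SD and ICC. Baseline adjustment could narrow the intervals, while dropout or fewer practices would widen them.

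This should be fixed but is not fatal. The sentence alters no primary outcome, randomisation, data collection or estimator.

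**What to change.** Delete the sentence in the phase two Analyses section and put in its place wording such as:

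> Between-group estimates will be reported with 95% confidence intervals for planning the definitive trial only. They will not be used to claim effectiveness or to decide that a definitive trial is unnecessary. Progression will be judged on the acceptability, feasibility and fidelity outcomes.

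This brings the section into line with the Sample size section and needs no new criterion. The 50% fidelity threshold under Amendments to intervention components should not be carried over, because it governs only the move from phase one to phase two. Nor should the 20 practices, or the average of 10 patients per practice that they imply, be turned into progression criteria. The first is a ceiling and the second is not stated as a phase two target.

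The cost is one sentence of protocol wording, with no change to data collection or analysis. The downside is that the option of an early effectiveness claim is given up.

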### Ethical Approval

A favourable ethical opinion for this study (protocol version 1.1) was granted by Sunderland Research Ethics Committee (application number 12/NE/0037). National Health Service (NHS) Research & Development approval was granted by NHS County Durham & Darlington. The trial was subsequently adopted by the CLRN portfolio to receive support from both the Diabetes Research Network (DRN) and Primary Care Research Network (PCRN).

## Discussion

PA/exercise is an integral part of diabetes management. However, the use of PA/exercise in routine clinical care for adults with Type 2 diabetes is hindered by the lack of acceptable, feasible and robustly evaluated interventions. Availability of such interventions will enable diabetes care providers to support their patients to increase and maintain their levels of free-living PA that are sufficient for achieving long-term glycaemic control.

The effective delivery of behavioural interventions is compromised by the lack of evidence-based training programmes to equip healthcare professionals with a range of intervention-specific competencies (knowledge and skills) and confidence to support adults with Type 2 diabetes to become more physically active in the long-term. A systematic review of 17 trials reported use of treatment fidelity measures in a majority of studies in terms of study design (for example, consistent duration and frequency of sessions across trial arms) and monitoring to improve receipt of intervention components and enactment of intervention–related knowledge and skills by patients [11]. In contrast, treatment fidelity strategies to monitor and improve provider training and delivery of treatment in practice were frequently omitted (for example, use of standardised training materials, observation of intervention implementation during training and video recordings of sessions with intervention providers and recipients). Training of intervention providers and treatment fidelity assessment are important for ensuring reproducibility of intervention-related skills in clinical practice and increasing the likelihood of implementation in routine clinical care [43,56].

The current study aims to address the above three barriers to facilitate use of PA as a management option for Type 2 diabetes in the routine primary care setting. MaMT2D is, to the best of our knowledge, the UK’s first online accredited training intervention programme to support primary healthcare professionals to develop the competencies to effectively deliver a primary healthcare professional-led intervention targeting the increase and maintenance of free-living PA in patients with Type 2 diabetes.

MaMT2D has been developed through a structured participatory design process, involving healthcare professionals and adults with Type 2 diabetes in the primary care setting working alongside psychologists, physiologists, designers and clinical experts. The theoretical underpinning of the multifaceted behaviour change intervention is evidence-based and the content informed by a systematic review of the evidence on behaviour change strategies and other intervention features used in behavioural interventions targeting free-living PA in adults with Type 2 diabetes. The approach used to develop the intervention maximises the likelihood that MaMT2D is acceptable and feasible for use by primary healthcare providers and patients in the clinical setting.

An open pilot design will allow opportunities for optimisation and refinement of study procedures and information content of both the online training intervention (primary healthcare professionals) and paper-based materials in the patient toolkit for use within the primary healthcare professional-led intervention in accordance with the preferences of primary healthcare professionals and patients. A subsequent external pilot cluster RCT (informed by the findings of the open pilot) and concomitant qualitative process evaluation and fidelity assessment will assess to what extent intervention components can be reliably and faithfully delivered in routine practice. Interval estimates of the mean difference between groups for the main outcome measures at each time point will be reported. Treatment fidelity strategies (use of standardised training, study manuals, ongoing process evaluation and video recording and assessment of patient sessions (intervention and usual clinical care)) will be utilised throughout the intervention period to serve two main purposes: 1) to ensure the intervention is being delivered according to the protocol; and 2) to identify any barriers to successful delivery of the intervention content and implementation in routine practice.

## Trial status

Recruitment of primary healthcare practices to MaMT2D commenced during July 2012. At the time of manuscript submission, twelve practices had provided informed written consent to participate and eleven had been randomised.

## Abbreviations

BCT: behaviour change technique; CLRN: Comprehensive Local Research Network; CONSORT: consolidated standards of reporting trials; DRN: Diabetes Research Network; HbA1c: glycated hemoglobin A1c; MaMT2D: Movement as Medicine for Type 2 Diabetes; NHS: National Health Service; PA: physical activity; PCRN: Primary Care Research Network; RCT: randomised controlled trial; SCT: social cognitive theory; SPIRIT: standard protocol items: recommendations for intervention trials; TDF: theoretical domains framework; TPB: theory of planned behaviour.
